### Who will take informed consent? {26a}

All informed consent discussions will be completed by a site-delegated study staff member, such as a research coordinator or research assistant.

### Additional consent provisions for collection and use of participant data and biological specimens {26b}

As per institutional guidelines, participants will be asked to complete a “Consent to Communicate by Email” form prior to completing the informed consent discussion. Participants will be asked permission to share their de-identified trial data in an open access database, in line with Canadian Institutes of Health Research (CIHR) best practice. This trial does not involve collecting biological specimens for storage.

## Interventions

### Explanation for the choice of comparators {6b}

Utilizing the NICE COVID-19 treatment guideline, we have selected a comparator group that will be able to answer the question “What is the clinical effectiveness of different service models of multimodality/multidisciplinary post-COVID-19 syndrome rehabilitation in improving patient-reported outcomes (such as quality of life)?” The comparator group will receive usual care and health coaching as required. We chose to compare this to health coaching plus electronic case management in the intervention group as this addresses one of the recommended research questions in the NICE guidelines “What is the clinical effectiveness of different service models of multimodality/multidisciplinary post-COVID-19 syndrome rehabilitation in improving patient-reported outcomes (such as quality of life)?”

### Intervention description {11a}

#### Control arm: health coaching plus usual care (HC)

##### Assessment

Participants randomized to the control arm will be offered assessment by a clinician, guided by the WHO Post COVID-19 CRF (https://www.who.int/publications/i/item/global-covid-19-clinical-platform-case-report-form-(crf)-for-post-covid-conditions-(post-covid-19-crf-)). This is a clinical tool developed by the WHO to guide and document the sequelae of COVID-19 and to ensure that clinical and rehabilitation needs are identified.

##### Investigation

Clinician judgment will be used to decide on further testing needed for clinical care.

##### Management

Control participants will receive a rehabilitation plan developed with their health professional that will be implemented in the 8 weeks after their initial consultation (baseline visit) and access to a personal health coach. The implementation will involve face to face or virtual care from a registered health professional provided by the clinic or research staff. This may be a combination of, but not limited to, occupational therapy, physical therapy, and/or social work/counselling services. The frequency of treatment visits will depend on the individual treatment plan after assessment. All participants will receive access to a health coach.

#### Experimental arm: electronic case management plus usual care

Participants randomized to the experimental arm will receive assessment, investigation and management as outlined above plus access to an electronic case management platform – NexJ Connected Wellness (https://nexjhealth.com/), supported by a personal health coach and which complements the rehabilitation plan. This would include, for example, setting targets for activity that would be monitored with NexJ; educational materials; and, support with medication adherence by reminders. The NexJ platform will include the following sections: Case Plans with Educational Workbooks, Trusted Educational Content (Health Library), Symptom Tracking, Goal Setting, and Reporting.

#### Timing of sessions

All participants will receive health coaching sessions up to once a week. Participants who are using NexJ will have assigned content between sessions. Due to the heterogeneous nature of Long COVID presentation, timing of clinical rehabilitation sessions will be individualized based on the treatment plan. This information will be recorded for each participant.

### Criteria for discontinuing or modifying allocated interventions {11b}

Decisions about modifying individual rehabilitation care or health coaching will be made in collaboration with the most responsible healthcare provider and the Principal Investigator. No predefined criteria will be used with respect to modifying individual interventions.

The trial will be stopped if more than 25% of participants in the intervention group experience at least a 20% increase in severity in their WHODAS sum score. There will be no stopping criteria for benefit given the short duration of the study.

### Strategies to improve adherence to interventions {11c}

No particular strategy will be implemented to improve adherence to the intervention as this is an outcome of the study. As part of the process evaluation, we are examining factors affecting adherence to the intervention. We will evaluate any differences in adherence between the treatment and intervention groups.

### Relevant concomitant care permitted or prohibited during the trial {11d}

As outlined in Table 1, only other trials providing treatment for Long COVID will be prohibited. All other concomitant care is permitted and will be documented.

### Provisions for post-trial care {30}

In the event of a study-related injury or illness, participants will be provided with appropriate medical treatment and care. Financial compensation for lost wages, disability, or discomfort due to an injury or illness is not generally available. After study completion, participants will not have access to the NexJ Connected Wellness platform as this is not publicly available. The participants’ most responsible care provider will ensure a transition back to or continuation of standard care, as required.

### Outcomes {12}

#### Primary outcome

To evaluate the primary outcome, improvement in quality of life, we will use the total sum score of the WHO Disability Assessment Scale (WHODAS 2.0) self-assessment. The WHODAS is a 36-item self-report questionnaire measuring health and disability from the previous 30 days across six domains of functioning: cognition, mobility, self-care, getting along, life activities, and participation. Responses are scored on a 5-point Likert scale: None [0], Mild [1], Moderate [2], Severe [3], and Extreme/Cannot Do [4] [32].

The WHODAS 2.0 has been validated using a cross-cultural approach in 19 countries and within 4 subgroups (general population, populations with physical problems, populations with mental or emotional problems, and populations with problems related to substance use). The WHODAS 2.0 showed excellent overall test-retest reliability (ICC=0.98) and internal consistency (Cronbach’s alpha = 0.98). The survey also showed good cross-cultural sensitivity and concurrent validity [32].

#### Secondary outcomes

##### Long COVID characteristics

To describe the population and their experience with Long COVID, we will administer the WHO Post COVID Case Report Form (CRF) Modules 1, 2, and 3 at baseline and only Module’s 2 and 3 at 12 weeks [33]. The CRF Module 1 captures demographics, pregnancy, pre-COVID health status, and details about the acute COVID infection. CRF Modules 2 and 3 collect vaccination status, occupational status, functioning, post-COVID symptoms, clinical tests, and scales (including neurological, radiographic, blood tests, heart and lung function, mental health, function, and musculoskeletal tests), new diagnoses or complications related to COVID infection, health service use, and symptoms [33]. The CRF will be completed using health record review whenever possible, with missing information completed by interview with the participant.

Currently, little is known about the long-term consequences of infection with COVID-19. In response to this, the WHO has created the WHO Post COVID Case Report Form, which will allow health care providers internationally to collect information on COVID-19 systematically. The use of this CRF will allow for the trial dataset to be aligned with the global WHO Clinical Platform and contribute to expanding our knowledge on Post-COVID-19 condition(s).

All other secondary outcome measures are described in Table 3.

**Table 3 Tab3:** Secondary outcomes

Measure	Description	Properties
Cognitive Testing	Executive function, visual attention, task switching	The Oral Trail Making Test (O-TMT) (versions A and B) will be used to evaluate executive function, visual attention, and task switching in participants. During O-TMT A, participants will be asked to count out loud from 1 to 25 and is primarily a measure of processing speed and simple attention. During O-TMT B, participants will be asked to alternate saying numbers and letters (1-A, 2-B, etc.) and is a measure of mental flexibility. Time to completion as well as total errors are recorded [34, 35]. The use of time and error rate led to slightly improved classification rates for cognitive impairments compared to either alone [36].
	Verbal learning and memory	The Hopkins Verbal Learning Test-Revised (HVLT-R) will be used to evaluate verbal learning and memory capabilities in participants [37]. The HVLT consists of a 12-item word list, composed of four words from each of three semantic categories. The list is read to participants at a rate of approximately 2 words per second. Participants are then asked to free recall the list of words. This is repeated for 3 trials. After the third trial and a 20–25-min delay (with no forewarning), participants will again be asked to free recall the 12 words and then will be read 24 words and asked to say “yes” after each word that appeared on the recall list (12 targets) and “no” after each word that did not (12 distractors) [38]. The HVLT is available in 6 forms to reduce test-retest learning effects, takes no more than 10 min to administer and is shown to be well tolerated by participants [37].
	Attention, Working memory	The Digit Span subset, a component of the Working Memory Index of the Weschler’s Adult Intelligence Scale - 4th Edition (WAIS-IV), will be used to assess attention and working memory [39]. Participants will be read a series of numbers and then asked to recall the numbers to the examiner in order (forward span), in reverse order (backward span), and in sequence (sequence span). Participants will complete spans of increasing length, with two trials at each length, until an error is made on both trials of a given length. Digit Span has shown good internal consistency and test-retest reliability across age groups [39, 40].
	Verbal fluency	The Phonemic and Semantic Verbal Fluency (or Controlled Oral Word Association Test [COWAT]) test will be used to assess verbal fluency. Participants will be given 1 min to produce as many unique words as possible: (1) within a semantic category (category fluency for Animals); and (2) starting with a given letter (letter fluency for letters F, A, and S). The COWAT has been shown to have sensitivity to brain lesions and conditions with impaired cognition (e.g., traumatic brain injury). Population norms are available for the COWAT for a broad age (16–95) and education (0–21 years) range [41, 42].
PHQ-9	Depression	A 9-item questionnaire that assesses the severity of depression symptoms experienced within the last 2 weeks. Participants are asked to rate each symptom of depression on a Likert scale from 0 (not at all) to 3 (nearly every day), with total scores ranging from 0 (minimal depression) to 27 (severe depression). The PHQ-9 has strong methodological properties with an internal consistency of 0.89 and strong test-retest reliability [43].
GAD-7	Anxiety	A 7-item questionnaire that assesses the severity of anxiety symptoms experienced within the last 2 weeks. The initial validation study, conducted by Spitzer et al. (2006), demonstrated high internal consistency (*α*=0.92) and test-retest reliability (intraclass correlation = 0.83) [44].
PSQI	Sleep	The Pittsburgh Sleep Quality Index (PSQI) is a self-report questionnaire that assesses sleep quality in the previous month and takes 5–10 min to complete. It has been translated into over 50 languages. Using a threshold score of greater than 5, the PSQI showed a diagnostic sensitivity of 89.6% and specificity of 86.5% (kappa = 0.75, *p* < 0.001) in distinguishing “good” and “poor” sleepers [45].
PSTD Checklist 5 (PCL-5)	Post-traumatic stress disorder	A 20-item self-report measure that assesses the presence and severity of PTSD symptoms, corresponding with DSM-5 criteria for PTSD. The PTSD Checklist 5 (PCL-5) scores exhibit strong internal consistency (*α* = .94), test-retest reliability (*r* = .82), and convergent (rs = .74 to .85) and discriminant (rs = .31 to .60) validity [46].
EQ-5D-5L	Quality of life	This is a 5-item questionnaire that assesses health-related quality of life, including mobility, self-care, ability to participate in one’s usual activities, pain or discomfort, and anxiety or depression and a visual analog scale (VAS) which asks participants to evaluate their overall health on a scale from 0 to 100. It is available in multiple languages, and there are standardized scores for patient populations in different settings. The EQ-5D-5L is able to define a unique health state based on the responses to each of the five dimensions of health described above [47].
AUDIT	Alcohol use	The AUDIT questionnaire is designed to assess alcohol consumption, drinking behavior, adverse reactions, and alcohol-related problems. Among those who were known to misuse alcohol, the AUDIT successfully detected an alcohol use disorder 99% of the time [48].
ASSIST	Alcohol and substance use	The ASSIST is a brief interview collecting information regarding use of tobacco, alcohol, cannabis, cocaine, amphetamine type stimulants, sedatives, hallucinogens, inhalants, opioids, and other drugs. Internal Consistency (Chronbach’s alpha) was over 0.80 for the majority of domains and good concurrent validity [49, 50].
FSS	Fatigue	The Fatigue Severity Scale (FSS) is a 9-item self-report that measures the severity and functional impact of fatigue. The scale demonstrated good internal consistency (Cronbach’s *α* 0.88), as well good test-retest reliability and sensitivity to clinical change [51].
Fatigue Numeric Rating Scale	Fatigue	A single-item patient-reported outcome, scored on a scale of 0–10, with good test-retest reliability (ICC=0.79, *p* < 0.008) and sensitivity to change [52].
Pain Numeric Rating Scale	Pain	The Pain Numeric Rating Scale will be used to assess pain intensity using a 0–10 ranking scale, where 0 represents “no pain” and 10 “unbearable pain.” The scale shows good test-retest reliability (ICC=0.72 for single item), and sensitivity [53]. Pain may be categorized using Mild (scores ≤5), Moderate (scores 6–7), or Severe (scores ≥8) [54].
MRC Dyspnoea Scale	Breathlessness	A 5-item self-report scale that evaluates statements of perceived breathlessness. The scale has good correlation to level of disability due to breathlessness [55].
WEMWBS	Wellbeing	The Warwick-Edinburgh Mental Wellbeing Scale (WEMWBS) (short version) is a 7-item scale which measures multiple aspects of mental wellbeing [56]. It has been validated in general population samples and in English and French [57], and is sensitive to change [58].

#### Predictors and potential confounders

At the first assessment, we will collect information on predictors and potential confounders as listed in Table 4.

**Table 4 Tab4:** Predictors, potential confounders and effect modifiers

Predictors and potential confounders	
Demographic details	At baseline, we will collect information on ethnicity, gender identity, education, income, employment, housing, and living circumstances
Past medical history	This will include body mass index and past medical and mental health disorders
Impact of COVID-19 infection	For those who tested positive, we will record details of the severity and impact of the COVID-19 infection including neurological symptoms such as anosmia and headaches, length of time self-isolating, and time off work
IEQ-SF	The Injustice Experience Questionnaire (IEQ) is a 12-item self-report that assesses perceived injustice associated with injury. The IEQ showed good correlation with measures of catastrophic thinking (*r*=.75, *p* <.01), fear of movement/re-injury (*r*=.58, *p*<.01), depression (*r*=.66, *p*<.01), and pain severity (*r*=.54, *p*<.01).The IEQ also demonstrated good test-retest reliability [59].
Adverse childhood events questionnaire (ACE)	The ACE-Q is a 17-item self-report questionnaire assessing types of adverse exposures during childhood including psychological, physical, and sexual abuse as well as household dysfunction. The ACE questionnaire study found strong relationships between childhood exposure and disease conditions, health risk factors, and a strong dose-response relationship between number of exposures and risk factors for death [60].

#### Process evaluation

To inform the implementation of the intervention beyond the clinical trial and describe the intervention process, we will use the RE-AIM framework [31]. We will assess Reach by recording what proportion of eligible patients participate in the trial and comparing characteristics of participants to non-participants. Effectiveness will be assessed in the clinical trial and separately stratified by sex. We will also record dropouts by sex and severity. We will conduct qualitative interviews with participants to better understand the reasons for participating, the experience of using the NexJ app, and any reasons for drop out. We will use a thematic analysis and aim to complete at least 20 user interviews and will continue until we achieve data saturation. We will gather usage data from NexJ. Adoption at the setting level will be assessed by comparing uptake in the different clinics supplemented by qualitative interviews with clinical staff. Adoption at the staff level will compare high referrers to the study to low referrers and doing qualitative interviews with staff in each group. Implementation will be assessed with a study specific-adherence scale. Maintenance at an individual and setting level will be assessed using the Consolidated Framework for Implementation Research (CFIR) to inform qualitative interviews with key stakeholders to identify barriers and facilitators to introducing NexJ in outpatient clinics.

#### Economic evaluation

We will conduct a cost-utility analysis of an electronic case management system compared with usual care from a perspective of the publicly funded health care system. Costs and outcomes will be assessed within the follow-up period of the trial. Resources and associated costs required to set up and operate a unique instance of the NexJ platform will be estimated from the budget review and staff interview. We will collect health care utilization data, such as hospitalization, emergency department visits, physician visits, prescriptions, and the efficacy of the intervention, from the concurrent trials. We will derive health utility value from the EQ-5D-5L using the Canadian validated algorithm [61], Quality-Adjusted Life Years (QALYs) will be estimated using the total area under the curve method [62]. Unit costs for each health care resource will be obtained from Canadian Sources. Costs will be expressed in 2021 Canadian Dollars.

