### Participant timeline {13}

Administration will occur as per the Time and Events Schedule in Table 5. Clinical visits will occur as needed and will be determined during the initial assessment. Clinical visits are not outlined in the time and event schedule as these are a part of routine care. Self-report measures will be completed at home prior to each study visit using the study Electronic Data Capture System (EDCS). Participants will be able to leave and return to the questionnaires whenever they need to complete them. It is anticipated the first and last visit will take approximately 45 min, while weeks 4 and 8 will take approximately 30 min. Participants will complete the WHODAS first and all responses are mandatory. All other self-report measures will be completed in a structured order.

**Table 5 Tab5:** Time and events schedule

Measures	Time to complete (minutes)	Administration	Baseline	Week 4	Week 8	Week 12
WHO Post COVID CRF Module 1	Variable	Chart review	**X**			
WHO Post COVID CRF Module 2	Variable	Chart review	**X**			**X**
WHO Post COVID CRF Module 3	Variable	Chart review	**X**			**X**
Demographics	<5	Self-report	**X**			
ACE-Q	5	Self-report	**X**			
Injustice Experience Questionnaire (IEQ-SF)	<5	Self-report	**X**			
WHODAS	5	Self-report	**X**	**X**	**X**	**X**
PHQ-9	<5	Self-report	**X**	**X**	**X**	**X**
GAD-7	<5	Self-report	**X**	**X**	**X**	**X**
PCL-5	5	Self-report	**X**	**X**	**X**	**X**
EQ-5D-5L	<5	Self-report	**X**	**X**	**X**	**X**
AUDIT	<5	Self-report	**X**			**X**
ASSIST	5-10	Interview	**X**			**X**
Fatigue Severity Scale	<5	Self-report	**X**	**X**	**X**	**X**
PSQI	5	Self-report	**X**	**X**	**X**	**X**
Warwick-Edinburgh Mental Wellbeing Scale (WEMWBS)	5	Self-report	**X**			**X**
Pain Numeric Rating Scale	<5	Self-report	**X**	**X**	**X**	**X**
MRC Dyspnoea Scale	<5	Self-report	**X**	**X**	**X**	**X**
Cognition (Trailmaking, Hopkins Verbal Learning, Digit Span, Phonemic/Semantic Verbal Fluency)	30	Interview	**X**			**X**
Qualitative Interview (Optional)	30	Interview				**X**

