## Assignment of interventions: allocation

### Sequence generation {16a}

Randomization will be done remotely by the Ottawa Methods Centre (OMC) through an electronic randomization system. Participants will be randomized at enrollment by a delegated study staff member. As participants are created in the ECDS, they are automatically randomized. The delegated study staff member will be informed of the allocation at the time of randomization.

Allocation will be a 1:1 ratio into the treatment arms. Participants will be stratified by sex and duration of symptoms. The reasons for stratification by sex are that the mortality rate in males is higher than in females and that outcomes may be affected by gendered occupations [63–66]. We will stratify by the duration of symptoms into two groups: (1) those who at enrolment have had symptoms since the onset of their index illness for 12 to 23 weeks, and (2) those who have had symptoms at enrolment for 24 weeks or longer, which is consistent with the classification of Long COVID in the NICE guidelines. We are stratifying for duration of illness as this is one of the main determinants of outcomes.

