#### Economic evaluation

Results of a cost-utility analysis will be presented as incremental cost per QALY gained. The incremental cost and incremental outcome will be estimated using generalized linear models that explicitly allow for the modelling of normal and non-normal distributional forms of data. The incremental cost-effectiveness ratio will be obtained through the difference in the mean costs of the two strategies divided by the difference in the mean QALYs for each strategy as denoted by the coefficient of the intervention indicator variables. Uncertainty in the analysis will be addressed by estimating 95% CIs using a non-parametric bootstrapping method. For this study, we will obtain 10,000 estimates of costs and outcomes for each strategy. Results from the bootstrapping exercise will also be used to show cost-effectiveness acceptability curves, which represent the probability of NexJ being cost-effective over a range of willingness to pay values that the health system may be willing to pay for an additional unit of QALY.

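### The incremental QALY is a contrast of total areas under the EQ-5D-5L utility curve with no baseline-utility adjustment named; adding the baseline already collected would remove avoidable noise at no cost

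*Protocol article*

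**What the plan says.** The Economic evaluation text under Outcomes {12} derives utilities from the EQ-5D-5L and says "Quality-Adjusted Life Years (QALYs) will be estimated using the total area under the curve method". The horizon is the trial itself: "Costs and outcomes will be assessed within the follow-up period of the trial", which is 12 weeks by Table 5.

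Table 5 (Participant timeline {13}) schedules the instrument at baseline and at weeks 4, 8 and 12: "EQ-5D-5L <5 Self-report X X X X".

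The Economic evaluation text under Statistical methods {20a} says "The incremental cost and incremental outcome will be estimated using generalized linear models that explicitly allow for the modelling of normal and non-normal distributional forms". The denominator of the cost per QALY is "the difference in the mean QALYs for each strategy as denoted by the coefficient of the intervention indicator variables". On uncertainty: "Uncertainty in the analysis will be addressed by estimating 95% CIs using a non-parametric bootstrapping method", using 10,000 estimates, which also feed cost-effectiveness acceptability curves.

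Neither text lists covariates for these models. Neither says that the models contain only the intervention indicator.

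Sequence generation {16a} says "Participants will be stratified by sex and duration of symptoms", so baseline utility is not balanced by design.

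**The concern.** A total area under the curve that starts at randomisation contains the baseline utility. A baseline difference between arms, which treatment cannot have caused, therefore forms part of the measured QALY difference. It also predicts later differences, because people with higher utility at baseline tend to have higher utility at later visits.

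Over a long horizon this may be minor next to the treatment effect. Over 12 weeks the whole QALY scale is 12/52 = 0.231 of a year, and a realistic gain is a few thousandths of a QALY. At this sample size, ordinary chance imbalance is of the same order.

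What is at stake is the precision of the denominator of the cost per QALY, and with it the acceptability curve, for the first key secondary objective. The primary outcome is not touched.

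**Working it through.** The article states no utility SD, correlation or expected QALY gain, so there is no figure of its own to reproduce. The check sizes the effect under stated assumptions.

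**Inputs from the article.** Visits at 0, 4, 8 and 12 weeks (Table 5). Recruitment of 76 per arm with 20% dropout (Sample size {14}): 76 × 0.8 = 60.8, taken as n = 61 per arm.

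**Assumed inputs.** Utility SD s = 0.2 at every visit (0.15 and 0.25 as alternatives). The same correlation r between any two visits, 0.5 to 0.8.

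**Weights.** The trapezoid rule gives w = (2, 4, 4, 2)/52 years, total 12/52. The baseline share is 2/12 = one-sixth.

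**Carry-over of a baseline gap d.** The expected shift in the QALY difference is d × c, with c = (2 + 10r)/52.
- r = 0.5: c = 0.1346. r = 0.8: c = 0.1923.
- SE of the chance gap: s√(2/n) = 0.2 × √(2/61) = 0.0362.
- Noise carried into the QALY difference: 0.0362 × 0.1346 = 0.0049 at r = 0.5, and 0.0362 × 0.1923 = 0.0070 at r = 0.8.

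**Standard error without adjustment.** SE = s√(2v/n), where v = Σw² + r[(Σw)² − Σw²] = 0.01479 + 0.03846r.
- r = 0.5: v = 0.03402, SE = 0.0362 × √0.03402 = 0.0067.
- r = 0.8: v = 0.04556, SE = 0.0362 × √0.04556 = 0.0077.

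**Standard error with baseline utility in the model.** SE = s√(2(v − c²)/n).
- r = 0.5: v − c² = 0.03402 − 0.01812 = 0.01590, SE = 0.0046.
- r = 0.8: v − c² = 0.04556 − 0.03698 = 0.00858, SE = 0.0034.

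The relative cut is 1 − √(1 − c²/v), with c²/v = 0.53 at r = 0.5 and 0.81 at r = 0.8. That is 32% to 57%, whatever the SD or sample size.

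**Size of a plausible gain (utility benefit of 0.05, assumed).**
- Building linearly to week 12: 0.05 × (4 × 1/3 + 4 × 2/3 + 2)/52 = 0.05 × 6/52 = 0.0058 QALY.
- Constant from week 4: 0.05 × (4 + 4 + 2)/52 = 0.0096 QALY.

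**Chance that the estimated QALY difference is zero or negative, Φ(−gain/SE), across r = 0.5 to 0.8.**

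| True gain | Unadjusted | Adjusted |
|---|---|---|
| 0.0058 | 19% to 23% | 10% to 4% |
| 0.0096 | 8% to 11% | 2% to 0.2% |

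**Sensitivity (r = 0.5 to r = 0.8).**

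| Case | SE unadjusted | SE adjusted |
|---|---|---|
| SD 0.15, n = 61 | 0.0050 to 0.0058 | 0.0034 to 0.0025 |
| SD 0.25, n = 61 | 0.0084 to 0.0097 | 0.0057 to 0.0042 |
| SD 0.20, n = 76 | 0.0060 to 0.0069 | 0.0041 to 0.0030 |

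The last row treats all 76 randomised per arm as fully informative, which is the best that multiple imputation could achieve.

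**The case against.** The strongest objection is that silence is not exclusion. A generalized linear model accommodates covariates, and an adjusted model also delivers its result as an intervention coefficient. The missing-data section {20c} speaks of imputing covariates, so some are expected somewhere. A condensed article may leave the covariate list to a full protocol or health-economic plan that is not shown. This stands. A reader might infer that the plan has decided against baseline adjustment; the text does not say so.

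Second, the harm is limited. Under randomisation the unadjusted difference is unbiased on average, and the bootstrap intervals and acceptability curves would show the lost precision as wider uncertainty. This also stands. A reader might infer that a baseline gap passes whole into the QALY difference or biases the analysis systematically. In fact one-sixth enters directly, the remainder depends on the between-visit correlation, and the only bias is conditional on the imbalance that happens to occur.

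Third, the magnitudes rest on assumed values, and the linear-build scenario is the less favourable of the two. The larger gain of 0.0096 roughly halves the chance of a wrong-signed unadjusted estimate. Even the adjusted analysis is not free of that risk, because the horizon is short and the sample small.

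Fourth, a reader might infer that the confidence interval is to be placed on the cost-per-QALY ratio itself. The article does not say this; it describes bootstrap intervals and acceptability curves without tying the interval to the ratio. No criticism is made on that score.

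What survives is narrower. The economic section settles the QALY method, model class, estimator and number of bootstrap estimates, yet does not name the covariate that matters most for an outcome with baseline built into it.

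**Conclusion.** The point holds as a free improvement, not as an error. Area under the curve is a sound QALY method, and the intervention coefficient is a sound place to read the increment. As written, however, the contrast can be carried out without baseline utility, and that version is materially less precise. With SD 0.2, equal correlation 0.5 to 0.8 and 61 per arm, the standard error is 0.0067 to 0.0077 rather than 0.0046 to 0.0034, against a plausible gain of about 0.006 to 0.010 QALY. The absolute figures move with the assumed SD and sample size. The relative cut of 32% to 57% depends only on the visit schedule and the assumed correlation structure.

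**What to change.** In the Economic evaluation text under Statistical methods {20a}, state that the QALY model includes baseline EQ-5D-5L utility and the randomisation strata (sex and symptom duration) as covariates. State that the incremental QALY is the adjusted intervention coefficient, and that the adjusted model is refitted in each bootstrap sample so that intervals and acceptability curves reflect it. If a fuller plan already specifies this, one clause in the article saying so is enough.

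The cost is a sentence. The baseline utility and both strata are already collected, the area-under-the-curve definition stays as it is, and the same 10,000-sample bootstrap is used.
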